# Feasibility and initial efficacy of a high-intensity interval training program using adaptive equipment in persons with multiple sclerosis who have walking disability: study protocol for a single-group, feasibility trial

**DOI:** 10.1186/s13063-020-04887-x

**Published:** 2020-11-25

**Keywords:** Multiple sclerosis, Adaptive equipment, Rehabilitation, Recumbent stepping, High-intensity interval training, Intervention, Feasibility, Exercise rehabilitation

## Abstract

**Background:**

There is considerable evidence for the efficacy of moderate-intensity continuous exercise benefitting clinically relevant outcomes in persons with multiple sclerosis (MS). However, persons with MS who have walking disability (pwMS-wd) are severely deconditioned and may achieve superior benefits by engaging in high-intensity interval training (HIIT), especially while utilizing adaptive equipment, such as recumbent arm/leg stepping (RSTEP). The proposed study will assess the feasibility of a 12-week, RSTEP HIIT program in pwMS-wd. The secondary aim will examine changes in aerobic fitness, physical activity, ambulation, upper arm function, cognition, fatigue, and depression as clinically relevant efficacy outcomes following the 12-week, RSTEP HIIT intervention.

**Methods:**

The study will recruit 15 pwMS-wd. Feasibility will be measured via process, resource, management, and scientific outcomes throughout the entirety of the research study. The secondary, clinically relevant outcomes will consist of a neurological exam, aerobic capacity, physical activity, ambulation, cognition, upper arm function, fatigue, and depression. Outcomes will be assessed at baseline (T1), midpoint (T2, following 6 weeks), and post-intervention (T3, following 12 weeks). The intervention will involve 12 weeks of supervised, individualized HIIT sessions two to three times per week. The individual HIIT sessions will each involve 10 cycles of 60-s intervals at the wattage associated with 90% VO_2peak_ followed by 60 s of active recovery intervals at 15 W, totaling 20 min in length plus 5-min warm-up and cool-down periods.

**Discussion:**

The feasibility design of the proposed study will provide experience and preliminary data for advancing towards a proof-of-concept study comparing HIIT to moderate-intensity continuous RSTEP for improving clinically relevant outcomes in a randomized control trial design. The results will be disseminated via manuscripts for publication and a report for distribution among the National Multiple Sclerosis Society.

**Trial registration:**

ClinicalTrials.gov NCT04416243. Retrospectively registered on June 4, 2020

## Background

Multiple sclerosis (MS) is a neurodegenerative disease of the central nervous system that results in clinical manifestations such as physiological deconditioning, cognitive dysfunction, and disruptions in mood [1]. One million adults are currently living with MS in the USA and upwards of 75% of those with MS report walking dysfunction that worsens with increasing disability [2–6]. Physiological deconditioning (i.e., reduced aerobic capacity) [7] is another hallmark of MS that worsens as a result of increasing disability [8], and undergirds many outcomes in MS. Accordingly, exercise training can target this cycle of physiological deconditioning and worsening disability [9] and may be a primary approach for slowing or reversing disability progression in persons with MS who have walking disability (pwMS-wd) [10]. Although there is considerable evidence for the efficacy of moderate-intensity continuous exercise (MICE) benefitting clinically relevant outcomes in persons with MS [11–16], pwMS-wd are severely deconditioned and may achieve superior benefits by engaging in high-intensity interval training (HIIT) [17–20], especially while utilizing adaptive equipment, such as with recumbent arm/leg stepping (RSTEP). RSTEP relies on similar motor activation patterns as walking [21, 22] and may increase walking performance in persons with neurological disability [21, 22], without the balance and safety risks of treadmill walking or application challenges with cycling (e.g., feet staying on pedals based on spasticity) that might affect pwMS-wd.

One systematic review summarized 7 published studies on HIIT in persons with MS [17] and identified that HIIT yielded significant improvements in cardiorespiratory fitness in all but one study [17]. Regarding studies that directly compared HIIT and MICE, the data indicated a potential superiority of HIIT for improving physiological conditioning in a time-efficient manner [17–20]. HIIT requires a shorter period of time for similar energy expenditure and may induce improvements in cardiorespiratory fitness through increases in stroke volume, maximal cardiac output, muscle capillarization, and mitochondrial content [23]. However, this evidence is specific among those with MS who have low disability engaging in cycle/arm ergometry, and the authors concluded that an investigation of HIIT in pwMS-wd is necessary as the feasibility and potential benefits are relatively unknown.

We recently published preliminary data identifying the acute effects of single sessions of high-intensity interval exercise (HIIE) as compared to MICE [24, 25]. The data indicate that a single bout of RSTEP HIIT taxed the cardiorespiratory system significantly more than MICE, yet without untoward effects on walking, gait, cognition, mood, or enjoyment [24, 25]. Those data were collected in pwMS-wd and suggested that RSTEP HIIT may be an acceptable, safe, and tolerable stimulus for chronic exercise training [26, 27]. Before moving on to a large-scale, randomized control trial (RCT), we must identify the feasibility and initial efficacy of chronic RSTEP HIIT for maximizing implementation strategies and long-term adherence with the exercise program. The feasibility data of the RSTEP HIIT program will identify if the intervention is practical through establishing the parameters of the design and to identify any potential threats to the validity of study outcomes [28]. Future iterations of the research study and design are then informed by the process, resource, management, and science outcomes, thus increasing the credibility of the next phases of research [28–31].

The proposed study will assess the feasibility of a 12-week, RSTEP HIIT program in pwMS-wd. Feasibility will be operationalized as process (e.g., recruitment, adherence, and retention rates), resource (e.g., time, space, equipment, and monetary costs), management (e.g., research training and preparation, strengths and weaknesses of expertise, and researcher capacity), and science (e.g., adverse events, participant burden, and participant feedback) outcomes [32]. We hypothesize that 12 weeks of HIIT will be feasible via process, resource, management, and scientific outcomes commensurate with other exercise interventions in multiple sclerosis (MS) [32, 33]. The study will further examine changes in aerobic fitness, physical activity, ambulation, upper arm function, cognition, fatigue, and depressive symptoms as clinically relevant efficacy outcomes following the 12-week, RSTEP HIIT intervention. We hypothesize that 12 weeks of HIIT will result in improvements in aerobic capacity, walking, upper arm function, cognition, fatigue, and depression. The clarity and strength of the proposed study stems from the primary focus on a feasibility design as opposed to conducting an initial pilot study, which emphasizes efficacy over practicality and design characteristics [28, 29, 34–37]. By documenting the study’s feasibility protocol in detail, we are able to provide valuable information to other scientists attempting to design and undertake feasibility trials before moving forward to a large-scale RCT [28].

## Methods

### Recruitment

The study will recruit 15 pwMS-wd (i.e., a PDDS score of 3–6) from areas surrounding Berry College. Berry College is located in a highly accessible, rural area in the northwest of Georgia. We will recruit from areas between Atlanta, GA; Chattanooga, TN; and Birmingham, AL. Participants will be asked to provide their own transportation to Berry College. With regard to the sample population, this study focuses on the effects of HIIT in those with MS who are ambulatory, but report walking impairments, as this represents upwards of 75% of the MS community. Although the proposed range of participants (i.e., PDDS scores of 3–6) is wide, all participants within this range report at minimum gait impairment and at maximum are primarily wheelchair users but are able to walk 25 ft in under 2 min. Using this wide range will allow us to answer our key question, while maximizing our recruitment potential in a rural, likely underserved population. We will examine medication use, symptoms of spasticity, and depression in the study results.

Recruitment will occur through fliers provided to local and regional MS Society chapters, clinics, and doctor’s offices; flyers provided at local and regional MS Society events; advertisements on social media; email communication to the local and regional MS Society participants; and by word of mouth. This study will be described as an opportunity to participate in a study testing physiological and functional responses to exercise in persons with MS. Participants will be asked to contact the laboratory by telephone or email for further information about the study and screening for inclusion. See Fig. 1 for a diagram of participant movement from recruitment through completion of the program and Fig. 2 for the schedule of enrollment, intervention, and assessments.

**Fig. 1 Fig1:**
[figure not shown]
Diagram of recruitment through completion of the program. *Note*: MS=multiple sclerosis, T1=baseline assessment, T2=midpoint assessment, T3=post-intervention assessment, RSTEP=arm/leg recumbent stepping, HIIT=high-intensity interval training, VO_2peak_=peak oxygen consumption achieved at either the baseline or midpoint assessment

**Fig. 2 Fig2:**
[figure not shown]
Schedule of enrollment, intervention, and assessments. *Note*: -T1=before baseline assessment, T1=baseline assessment, T2=midpoint assessment, T3=post-intervention assessment, MS=multiple sclerosis, RSTEP=arm/leg recumbent stepping, HIIT=high-intensity interval training

### Screening, eligibility criteria, and retention

#### Inclusion criteria

Participants who meet the following criteria will be included: (a) age 18–64 years, (b) a self-reported diagnosis of MS, (c) self-reported Expanded Disability Status Scale (EDSS) score < 8.0 or Patient Determined Disability Steps (PDDS) scale score ≤ 7.0, (d) relapse free in past 30 days, (e) willing and able to visit Berry College on three testing occasions and twenty-four training occasions, (f) asymptomatic status for maximal exercise testing, (g) physician approval for undertaking exercise testing, and (h) a self-reported ability to speak, read, and understand English. Participants who do not meet those criteria will be excluded from study participation. Age, self-reported MS diagnosis, relapse status, and willingness to visit Berry College’s campus will be assessed using a simple checklist. Confirmed MS diagnosis will be based on a letter from the participant’s neurologist. Disability status will be determined using the self-reported EDSS and the PDDS scale. Asymptomatic status is defined as one or fewer affirmatives on the Physical Activity Readiness-Questionnaire (PAR-Q). MS verification and medical clearance for exercise testing will be provided by the participant’s physician.

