#### Screening procedure

Inclusion criteria will be assessed over the telephone or in-person by [name], the research coordinator, or trained undergraduate research assistants. All screening personnel will undergo training prior to data collection to ensure all screening will be administered according to standardized instructions. There is no special expertise required to make inclusion/exclusion decisions. At first contact with potential participants, screening personnel will provide a description of the study using a telephone script. Potential participants will then be screened for age, diagnosis of MS, relapse status, willingness to visit Berry College on 27 occasions, disability status, asymptomatic status, and ability to speak, read, and understand English. Potential participants who meet these criteria will be sent forms for documenting the confirmed diagnosis of MS and obtaining medical clearance for exercise testing. Final decisions regarding participant inclusion will be made only once all screening materials have been received and reviewed. [name] will make final decisions on participant inclusions/exclusion. We will retain screening data for those who qualify and volunteer to participate and destroy screening data from those who do not qualify or do not volunteer.

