## Discussion

The proposed study evaluates the feasibility and preliminary efficacy of a 12-week, HIIT program using RSTEP in pwMS-wd (i.e., a PDDS score of 3.0-6.0). This work is driven by preliminary data indicating that an acute bout of HIIT taxes the cardiorespiratory system significantly more than continuous exercise, yet without sustained deleterious effects on walking, gait, cognition, core temperature, mood, or enjoyment in pwMS-wd [24, 25]. Those pilot data are from an acute or single bout of HIIT and suggest that the stimulus is acceptable, safe, and tolerable for inclusion in a chronic exercise-training program.

The proposed study will be the first to evaluate the feasibility of a 12-week HIIT program using adaptive equipment for pwMS-wd. A “feasibility study” informs the pragmatics of a RCT by defining whether an intervention can be done, should we continue with the proposed line of inquiry, and if so, how do we proceed to the RCT [53]. Process, resource, management, and science feasibility outcomes are critical to determining if an intervention is viable or not [28, 32]. Moreover, ideal participant recruitment, participant adherence, staff training, protocol execution, and data management strategies can be established. This is crucial for future research on HIIT exercise in MS. The use of a priori Go/No Go Criteria for advancement to a RCT further contributes to the strength and clarity of the proposed design. Such an initial examination of HIIT for inducing physical and functional improvements in pwMS-wd aims to reduce burdens of disability and use objective markers of progress and real-world outcomes.

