The proposed study is not without limitations. The first relates to the absence of a control group. No control group will be used because we specifically aim to identify the feasibility and preliminary efficacy of the HIIT exercise protocol alone in pwMS-wd. Once the intervention has been deemed safe and scientifically efficacious through meeting the Go/No Go Criteria set forth in the proposed study design, future iterations of the study will include a control group engaging in MICE. Another limitation to the current study is that it is lab-based and requires that participants provide their own transportation. All efforts will be made to coordinate transportation with participants, including the use of para-transit services within the immediate area. Transportation will be included as a possible reason for declining participation in the study during recruitment. Finally, the inclusion/exclusion criteria limit the generalizability of the study to those who have MS, report walking dysfunction but are able to walk 25 ft, and are under the age of 65. Although the proposed range of participants (i.e., PDDS scores of 3–6) is wide, all participants within this range report at minimum gait impairment and at maximum are primarily wheelchair users but are able to walk 25 ft in under 2 min. Using this wide range will allow us to answer our key question, while maximizing our recruitment potential in a rural, likely underserved population.

As a new rehabilitative approach, HIIT has led to significant benefits in persons with MS who have mild disability, other clinical populations, and healthy populations [18, 19, 56, 60, 61]. HIIT presents a paradigm challenge for pwMS-wd, however, as this population seemingly should not engage in high-intensity exercise—our published pilot data challenge that paradigm as will the proposed research. The proposed research may create a shift among exercise rehabilitation programs for pwMS-wd that is synonymous with the exercise revolution that occurred in cardiac care [62] by demonstrating that a HIIT intervention is feasible and provides a significant stimulus to successfully condition severely deconditioned pwMS-wd. Future studies may generate data on the effects of HIIT in pwMS-wd on motor learning capacity and possible alterations to brain structure and integrity.

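### Inclusion criterion (c) sets only upper disability limits and no walking requirement, which contradicts the stated population of PDDS 3–6 able to walk 25 ft

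*Protocol article*

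**What the plan says.** The protocol article describes who is to be studied in four places.

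- **Recruitment:** "The study will recruit 15 pwMS-wd (i.e., a PDDS score of 3–6) from areas surrounding Berry College". The same section describes the range as running from gait impairment at the mild end to people who mainly use a wheelchair but can still walk 25 ft within 2 minutes.
- **Discussion, opening paragraph:** the study concerns a "HIIT program using RSTEP in pwMS-wd (i.e., a PDDS score of 3.0-6.0" range, the same limits again.
- **Discussion, limitations paragraph:** the inclusion and exclusion criteria are said to confine the study to people who have MS, "report walking dysfunction but are able to walk 25 ft, and are under the age of 65".
- **Inclusion criteria:** the list opens with "Participants who meet the following criteria will be included". Its disability item, criterion (c), is a "self-reported Expanded Disability Status Scale (EDSS) score < 8.0 or Patient Determined Disability Steps (PDDS) scale score ≤ 7.0".

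On how disability is established for entry, the Inclusion criteria section says: "Disability status will be determined using the self-reported EDSS and the PDDS scale". The Screening procedure section has staff ask about age, diagnosis and relapse status, then "willingness to visit Berry College on 27 occasions, disability status, asymptomatic status, and ability to speak, read, and understand English". It names no PDDS range and no walking check.

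**The concern.** The list that decides entry and the population the article says it studies are different sets of people. Criterion (c) has ceilings only, the ceilings are joined by an 'or', and the PDDS ceiling lies above the top of the stated range. A volunteer with no walking disability meets it, and so does one at PDDS 7.

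The Background justifies the trial by saying that existing evidence on high-intensity interval training in MS comes from people with low disability. The written list readmits that group. The trial's main product is a Go/No Go decision about a randomised trial in people with walking disability. If some of the 15 are outside that group, the decision is partly about someone else.

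**Working it through.** **1. The plan's own figures.** Data analysis sets the first Go criterion at 80% of participants: 0.80 × 15 = 12. Each must complete 20 of 24 sessions: 20/24 = 83%. The 27 visits in Screening procedure equal 3 testing + 24 training. All reproduce.

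**2. The claimed limits against the list.** The limitations paragraph names four restrictions. Checked against criteria (a) to (h):

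| Restriction claimed in the Discussion | Criterion that imposes it |
|---|---|
| Has MS | (b), plus the neurologist's letter |
| Under 65 | (a), age 18–64 |
| Reports walking dysfunction | none; (c) has no lower limit |
| Able to walk 25 ft | none |

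The remaining items, (d) to (h), cover relapse, visits, asymptomatic status, physician approval and language. None bears on walking. The timed 25-ft walk and the examiner-administered EDSS appear only under Outcome assessments, not as entry conditions.

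**3. Which scores differ.** The article does not give the full PDDS range, so I assume whole-number steps from 0. The PDDS limb then admits 0 to 7 and the stated population is 3 to 6. Scores 0, 1, 2 and 7 are therefore admitted but off target. The 'or' also lets a person enter on self-reported EDSS below 8.0 whatever the PDDS score.

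**4. What this could do to the first Go criterion.** Let k of the 15 be off target.

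- In-target participants number 15 − k. At k = 4 this is 11, fewer than 12, so from there on any Go must count at least one off-target completer.
- With completion probability p in target and q off target, P(Go on criterion 1) = P(X + Y ≥ 12), where X ~ Bin(15 − k, p) and Y ~ Bin(k, q).

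| Assumed p, q | k = 0 | k = 3 | k = 5 |
|---|---|---|---|
| 0.70, 0.95 | 0.30 | 0.46 | 0.58 |
| 0.85, 0.60 | 0.82 | 0.65 | 0.52 |

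All values of p, q and k are assumptions. The 0.85 borrows the stated dropout of about 15%, which is not the same as completing 20 of 24 sessions. The table shows only that the shift can go either way. The contradiction in step 2 does not depend on it.

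**The case against.** The best defence is that the 3–6 range is not confined to the Discussion. Recruitment, within Methods, states it and argues for it. Screening collects disability status, and one person makes the final inclusion decision after reviewing all materials. The exercise-test increments are given only for cane and walker users, so the procedures presuppose walking disability. Criterion (c) may be a loosely copied ceiling that staff never apply literally. The recruitment diagram (Fig. 1) is not shown and may carry the range. Disability will also be examined by a certified assessor, so off-target entrants should be visible afterwards. This makes off-target enrolment less likely, but two rules remain in print, and the one that says who will be included is the wider.

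The defence is right against several stronger readings that a reader might infer:

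- **Milder participants would raise adherence and fitness gains.** No figure in the article supports this. On fitness, the Background leans the other way: it suggests that the severely deconditioned may gain more.
- **PDDS 7 would leave walking outcomes missing or at floor.** The article does not define PDDS 7. It already places people who mainly use a wheelchair within 3–6, and the 6-minute walk allows devices and rests.
- **A wider sample would inflate the half-SD threshold.** Data analysis does not say which standard deviation is meant.
- **Half the admitted scale levels are off target, or one person is 6.7% of 15.** Counting levels says nothing about how many people enrol at them, and under a 12-of-15 rule any participant can be decisive.
- **The 2-minute walk is an omitted entry test.** The article gives it as a description of the range, not as a criterion.

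**Conclusion.** The contradiction stands. Criterion (c), as written, does not select the PDDS 3–6 population of Recruitment and the Discussion. The limitations paragraph credits the criteria with two walking limits that they do not contain. This is a conflict between statements in the article, not detail left to a fuller protocol, because the article prints the list and says that those who meet it will be included.

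The consequence is a possibility. Feasibility and Go/No Go results could rest partly on people outside the target; their number, and the direction and size of any effect, cannot be determined from the documents. A reader might conclude that the trial will answer its question in the wrong people. The text does not support that, since recruitment is aimed at 3–6 and the range may be applied in practice. The finding rests on the wording alone; the PDDS step range and the completion rates above are assumptions used only for illustration.

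**What to change.** Reconcile Recruitment, Inclusion criteria, Screening procedure and both Discussion statements, so that the operative criterion and the screening checklist match the stated population. Which limits are intended is for the investigators to decide:

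- If PDDS 3–6 with ability to walk 25 ft is intended, as Recruitment and the Discussion indicate, write both into criterion (c) and remove the EDSS alternative that bypasses them. EDSS can stay as a descriptor.
- If the wider list is intended, correct the population statements and the limitations paragraph instead.

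Trial status reports 6 enrolled at June 12, 2020, so 15 − 6 = 9 of the planned places were then still open to a corrected rule. For those already enrolled, report PDDS and give the Go/No Go result with and without anyone outside 3–6, stating the denominator. For example, with one person excluded, 0.80 × 14 = 11.2, so 12 of 14 would be needed.

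The cost is a short amendment and a checklist edit. PDDS is already collected at screening, and recruitment would be no narrower than the stated target.
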